## Abstract

**Background:**

Individual Placement and Support (IPS) appears to be an effective vocational intervention for obtaining competitive employment for people with severe mental illness. However, no IPS studies or trials have been conducted in Denmark, a country characterized by a specialized labor market with a higher minimum wage and fewer entry-level jobs in comparison with other countries such as the US. Furthermore, long-term job retention and economic self-sufficiency have not been clearly demonstrated. Integrating methods such as cognitive remediation and work-related social skills training may be ways to address these issues.

**Methods/Design:**

The trial design is an investigator-initiated, randomized, assessor-blinded, multi-center trial. A total of 750 patients with severe mental illness will be randomly assigned into three groups: (1) IPS, (2) IPS enhanced with cognitive remediation and work-related social skills training, and (3) service as usual. The primary outcome is number of hours in competitive employment or education at 18-month follow-up. Secondary and exploratory outcomes are money earned, days to first employment, symptoms, functional level, self-esteem, and self-efficacy at 18-month follow-up. Thirty- and 60-month follow-ups will be register-based.

**Discussion:**

This will be one of the largest randomized trials investigating IPS to date. The trial will be conducted with high methodological quality in order to reduce the risk of bias. If the results of this trial show that IPS, or IPS enhanced with cognitive remediation and work-related social skills training, is superior to service as usual, this will support preliminary evidence. Furthermore, it will show that the method is generalizable to a variety of labor markets and welfare systems and provide important knowledge about the effect of adding cognitive remediation and social skills training to the IPS intervention.

**Trial registration:**

ClinicalTrials registration number: NCT01722344 (registered 2 Nov. 2012).

## Background

People with severe mental illnesses, defined as psychotic disorders, bipolar disorders, or major depression, identify employment or education as a key component to their recovery process, and approximately 65 % endorse employment as a goal [1–3]. However, employment seems to be a challenge in this population in which previous research has estimated a global unemployment rate of up to 90 %, which results in both personal and socioeconomic costs [4, 5].

Conventional vocational rehabilitation programs meet these challenges by employing a “train and place” approach, emphasizing prevocational training such as sheltered employment or trainee placements [1]. This approach remains the most widespread but has been shown to have very poor effects on competitive employment as well as low rates of client retention [6, 7].

In contrast, Individual Placement and Support (IPS) follows a “place and train” philosophy, which consists of an individualized and rapid search for competitive employment or education, avoiding prolonged prevocational training and preparation [8–10]. The intervention is integrated within the mental health services with emphasis on client preferences and choice regarding jobs and includes ongoing job support and benefit counseling [8–10].

The effects of the IPS intervention have been investigated in a number of randomized clinical trials, and reviews of these trials suggest that IPS is superior to other types of vocational rehabilitation programs in regard to obtaining competitive employment [6–9]. A review including 15 high-fidelity IPS trials shows an average employment rate among the IPS participants of 58.9 % compared with 23.2 % for control participants [7]. All of the control groups consisted of either treatment as usual, typically referral to the state vocational system, or well-established alternative vocational models [7]. Outcomes related to wages earned and hours worked were also found to be superior among those receiving the IPS intervention [7]. Previous research has not found that IPS leads to increased stress, exacerbation of symptoms, or other harmful clinical outcomes [8, 10]. The results of a recent Cochrane systematic review investigating IPS-supported employment for adults with severe mental illness additionally suggest that, compared with other vocational approaches, IPS is effective in improving a number of vocational outcomes relevant to people with severe mental illness [11]. However, the authors conclude that evidence from the included randomized trials was of “very low quality” mainly due to a high risk of bias (i.e., not describing allocation concealment). Furthermore, the meta-analysis excluded a majority of previous trials because of skewed data and populations of fewer than 200 people [11].

Moreover, it has been suggested that long-term job retention and economic self-sufficiency could be further improved by adding cognitive remediation and work-related social skills training to the intervention [10, 11]. Impairment in these functions is frequent among persons receiving IPS services and is known to be related to employment outcomes in persons with severe mental illness [12–14]. Two small-scale trials have found improved effects when the intervention was enhanced with either cognitive remediation or work-related social skills training [13, 15–17].

Randomized clinical trials of IPS have been conducted in different socioeconomic and cultural contexts with different results. A review found that four of five trials with the lowest employment rates were non-US trials [7]. Furthermore, a randomized trial from the UK investigating IPS compared with service as usual did not show significant vocational effects [18]. The authors suggest that implementation of IPS in labor markets and economies where economic disincentives may lead to lower levels of motivation can be challenging [18]. Until now, IPS trials have not been conducted in Denmark, where barriers to implementation and replication of previous international findings may exist. Firstly, Denmark is characterized by complex employment legislation and a highly specialized labor market with a high minimum wage and few entry-level jobs, which could impact both the implementation of IPS and potential effect sizes. Secondly, the social security system is generous compared with those of other countries, and this may be a perceived or real financial disincentive for returning to competitive employment and hence influence motivation levels [18, 19].

Thus, it is crucial to investigate whether IPS can be implemented in Denmark, and a large-scale trial with low risk of bias and a long follow-up period is needed. The present trial will be the largest randomized clinical trial to date to investigate the effects of IPS and IPS enhanced with cognitive remediation and work-related social skills training. The primary outcome is number of hours in competitive employment or education at 18-month follow-up.

## Methods/Design

### Trial design

The trial is designed as an investigator-initiated, randomized, three-arm, assessor-blinded, multi-center trial. A total of 750 patients with severe mental illness will be randomly assigned into (1) IPS, (2) IPS enhanced with cognitive remediation and work-related social skills training, and (3) service as usual.

The primary hypothesis is that participants allocated to the IPS intervention group (group 1) will have significantly higher work or study rates at 18-month follow-up compared with participants allocated to service as usual (group 3). Furthermore, we assume that an enhancement of the IPS intervention with cognitive remediation and work-related social skills training (group 2) will increase the effects. To ensure high methodological quality, the trial is designed and reported according to the SPIRIT (Standard Protocol Items: Recommendations for Interventional Trials) Statement and the modified CONSORT (Consolidated Standards Of Reporting Trials) criteria for non-pharmacological trials [20, 21].

### Recruitment and eligibility criteria

Eligible participants are adults (ages 18–67) diagnosed according to the International Classification of Diseases version 10 (ICD-10) with schizophrenia, schizotypal, or delusional disorders (F20–F29); or bipolar disorder (F31); or severe depression (F33). Participants must reside in one of two major Danish cities: Copenhagen (including the municipality of Frederiksberg) or Odense. They must be assigned to early intervention teams (OPUS teams) or community mental health services at Mental Health Center Copenhagen or the Department of Mental Health Odense-University Clinic. They must express a clear desire for competitive employment or education and provide verbal and written informed consent. Furthermore, participants must be able to speak and understand Danish well enough to participate without an interpreter, mainly in order to benefit from the group-based cognitive remediation therapy. A connection to vocational authorities with a formalized collaboration with the IPS teams is the foundation for the residence criterion. If this criterion leads to an insufficient number of patients, expansion of the geographic area of the trial will be considered. Participants who are interested in competitive employment or education are identified by case managers, who assess for eligibility and refer to the trial. To ensure that the participants meet the diagnostic criteria, they will be assessed by a trained and certified research assistant using the Schedules for Clinical Assessment in Neuropsychiatry (SCAN) diagnostic tool [22]. Informed consent will be obtained from each participant before assessment.

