### Randomization

After the assessment, a central web-based randomization will be performed by the Copenhagen Trial Unit [23] according to a computer-generated allocation sequence with permuted blocks of varying sizes. The allocation sequence and varying block sizes will be concealed from the investigators. A research secretary will perform the allocation by logging on to a website by using a personal password. Previous research has shown an effect of sex and of work history on vocational outcomes [24, 25]. Therefore, the allocation sequence will be stratified by sex and by work history (more or less than 2 months of competitive employment during the last 5 years). Furthermore, participants will be stratified by work readiness by using match categories, a tool used in Danish job centers [26]. We will assess the likelihood that the participant is ready to apply for competitive employment and will be self-sufficient within 3 months (match 2 or 3). Finally, the participants will be stratified by site.

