Employment specialists in Copenhagen are employed by the vocational authorities in the municipality (job centres) but will still be integrated within the mental health services.

It is expected that many of the participants in the trial will have an aim or motivation to start or resume education. This is expected, firstly, because many of the participants will be young adults recruited from early intervention teams (OPUS) and, secondly, because the education system in Denmark is financed by the state or the municipalities without tuition fees and with the opportunity to receive financial support from the State Educational Grant and Loan Scheme (SU). These options give employment specialists greater opportunities to focus on education compared with previous IPS reports. Employment specialists are encouraged to closely follow the methods described in the updated and expanded IPS manual “Applying the individual placement and support (IPS) model to help clients compete in the workforce” [27]. The manual, including worksheets, is translated into Danish, and the two IPS teams will be trained in the method by an IPS expert, who will also offer tele-supervision throughout the trial period. The IPS employment specialists will be evaluated by trained external reviewers who will use the IPS fidelity scale to ensure high fidelity and adherence to evidence-based practice [28]. The evaluation will take place 6 months after trial start and thereafter every sixth month until high fidelity is demonstrated. Subsequently, an annual evaluation will be performed.

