### Data analysis plan

The main null hypothesis to be tested is that there is no difference between the three groups in hours in competitive employment or education in the 18-month follow-up period. All randomized participants will be analyzed, including those who stop receiving treatment, according to the intention-to-treat principle. All continuous outcome measures, including the primary outcome “hours in competitive employment or education”, will be analyzed by using generalized linear models. In situations in which the continuous measure is non-normally distributed, a non-parametric model will be used. Multiple imputations will be used to impute a distribution of missing values. Furthermore, linear mixed models with repeated measurements and unstructured covariance matrixes will be used to assess the potential interaction between time and intervention. The dichotomous secondary outcome “work or education at some point during the follow-up period” will be analyzed by using logistic regression. The secondary outcome “time-to-employment or education” will be analyzed by using the Cox proportional hazards model. All models will be adjusted for the stratification variables.

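### Service type (OPUS or community team) and age are outside the stated adjustment set although the protocol links OPUS recruitment to study: a small possible loss of precision that is cheap to recover

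*Protocol article*

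**What the plan says.** The section on recruitment and eligibility admits adults aged 18 to 67 through two routes: "They must be assigned to early intervention teams (OPUS teams) or community mental health services at Mental Health Center Copenhagen or the Department of Mental" (the sentence ends with the Odense clinic).

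Under Group 1 – IPS, the article expects many participants to want to start or resume education. It gives two reasons. One is that "many of the participants will be young adults recruited from early intervention teams (OPUS"). The other is that education in Denmark has no tuition fees and comes with state grants.

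Under Outcome and assessments, the primary outcome adds up hours in competitive employment or education from baseline to 18 months.

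Under Randomization, "the allocation sequence will be stratified by sex and by work history (more or less than 2 months of competitive employment during the last 5" (the closing figure counts years). In addition, "participants will be stratified by work readiness by using match categories", and "Finally, the participants will be stratified by site". Service type and age are not in the list.

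Under Data analysis plan, continuous outcomes "will be analyzed by using generalized linear models", with a non-parametric model where the data are not normal. On covariates the section says only this: "All models will be adjusted for the stratification variables".

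**The concern.** Service type is fixed before randomization and known for everyone, because it is an entry criterion. The protocol itself connects one of the two services with an orientation towards study, and study hours count in the primary outcome.

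The stratifiers do not obviously capture this. Work history is defined by months of competitive employment. Match category is defined by readiness to apply for competitive employment and become self-sufficient. A young OPUS patient about to resume education and an older community patient long out of work could fall in the same stratum. Site, read as Copenhagen or Odense, would not separate them either.

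If mean hours differ between the services, that difference stays in the residual variance of the primary model, and the intervals are wider than they need to be. Precision is all that is at stake.

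**Working it through.** **Inputs from the protocol article** (Sample size and power calculation): difference 150 h, SD 500 h, type I error 0.0125 per comparison, power 80 %, 250 per group. The test is taken as two-sided, because the null is stated as equality of means; a one-sided test would need only 212 per group.

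**Step 1: reproduce the plan's figure.** n per group = 2 × (SD/difference)² × (z for 0.0125 two-sided + z for 80 % power)² = 2 × (500/150)² × (2.498 + 0.842)² ≈ 248, against 250 stated. At 250 per group, the standard error is 500 × √(2/250) = 44.72 h. Normal-approximation power is 0.804, and exact t power is 0.801. The fallback of 236 per group at 0.0167 also reproduces (233 computed). The design therefore meets its stated power without any covariate gain.

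**Step 2: effect of adding service type.** Let p be the OPUS share and D the difference in mean hours between services within an arm. The documents give neither, so both are assumptions. The share of variance explained is R² = p(1 − p) × D²/500², and the residual SD is 500 × √(1 − R²). For example, p = 0.5 and D = 200 give R² = 0.25 × 40,000/250,000 = 0.04 and a residual SD of 489.9 h.

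| Assumed gap D | R² (p = 0.2 to 0.5) | Power at 250 per group | n per group for 80 % |
|---|---|---|---|
| none | 0 | 0.804 | 248 |
| 50 h | 0.2 to 0.3 % | 0.805 | 248 |
| 100 h | 0.6 to 1.0 % | 0.807 to 0.809 | 247 to 246 |
| 200 h | 2.6 to 4.0 % | 0.816 to 0.823 | 242 to 238 |
| 300 h | 5.8 to 9.0 % | 0.831 to 0.846 | 234 to 226 |

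The gain is about 0.1 to 2 power points for gaps of 50 to 200 h. It is about 3 to 4 points at 300 h, which is twice the target treatment effect. These are upper bounds, because sex, work history, match category and site are already in the model and may explain part of the gap. No separate calculation was made for age.

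**Step 3: chance imbalance.** Under simple randomization, the OPUS share would differ between two arms with an SD of √(p(1 − p) × 2/250), that is 3.6 to 4.5 percentage points. At p = 0.5 and D = 300 this is 0.0447 × 300 ≈ 13 h, against a standard error of 44.72 h. In variance terms, (13.4/44.72)² ≈ 0.09, which is the R² in the last row of the table. Imbalance and wider intervals are the same loss and must not be counted twice.

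**The case against.** The strongest reply is that nothing here is an error. Adjusting for the stratifiers is sound. The sentence on adjustment does not say that only these variables will be used, and further prognostic covariates are often left to an analysis plan, which is not shown. This stands: the point is an improvement to the covariate set as stated, and it corrects no mistake.

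The second reply is that the link to the outcome is thinner than it looks. A reader might infer that the protocol predicts different hours in the two services. It does not. It speaks of aims and motivation, gives the funding of education as a second reason, and compares neither education hours nor total hours between services. More study in OPUS could be offset by less work. Nor do the documents support the inference that education makes up half of the outcome: it is one of two components, and no share is given. Both cautions stand, and they are why the gap is treated as unknown down to 50 h.

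Third, the calculation is for a linear model of hours. In logistic and Cox models, adding prognostic covariates changes the odds or hazard ratio being estimated and does not simply narrow its interval. The non-parametric fallback is not specified closely enough to compute a gain. This also stands and limits the recommendation.

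Fourth, a fifth binary stratifier would double 2 × 2 × 2 × 2 = 16 strata (with two sites) to 32, so the average stratum would fall from about 47 to 23 participants. That argues against stratifying on service type. It does not argue against a covariate.

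**Conclusion.** The point holds as a minor efficiency gain. The adjustment set as stated leaves out a baseline variable that is known for every participant and that the protocol connects with one component of its primary outcome.

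A reader might conclude that the comparison is biased or the trial underpowered. The documents support neither conclusion: randomization makes any imbalance in service type unbiased in expectation, and 250 per group reproduces the stated 80 %.

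The likely gain is about 0.1 to 2 power points for gaps of 50 to 200 h, and more only if the services differ by well over the target effect. This rests on an assumed OPUS share of 20 to 50 %, assumed gaps, the plan's SD of 500 h, a linear model and no overlap with the existing stratifiers.

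**What to change.** Before unblinding, prespecify service type at randomization (OPUS or community team) and age as additional fixed covariates in the primary model for hours, alongside the stratification variables. Leave the randomization as it is. Make no claim of added precision for the logistic, Cox or non-parametric analyses.

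Separately, report employment hours and education hours by service type in a descriptive table labelled exploratory. Covariate adjustment cannot show whether a difference in total hours comes from study or from work; such a table can at least describe it.

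The cost is a sentence or two in the analysis plan, two model terms and one table. Service type and age are already held from the eligibility check, so no new patients or procedures are needed. The Trial status section reports 480 of the planned 750 participants randomized by January 2015, so recruitment was still under way when the article was written.

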### Randomization

After the assessment, a central web-based randomization will be performed by the Copenhagen Trial Unit [23] according to a computer-generated allocation sequence with permuted blocks of varying sizes. The allocation sequence and varying block sizes will be concealed from the investigators. A research secretary will perform the allocation by logging on to a website by using a personal password. Previous research has shown an effect of sex and of work history on vocational outcomes [24, 25]. Therefore, the allocation sequence will be stratified by sex and by work history (more or less than 2 months of competitive employment during the last 5 years). Furthermore, participants will be stratified by work readiness by using match categories, a tool used in Danish job centers [26]. We will assess the likelihood that the participant is ready to apply for competitive employment and will be self-sufficient within 3 months (match 2 or 3). Finally, the participants will be stratified by site.

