### Outcome and assessments

The primary outcome is “hours in competitive employment or education” measured from baseline to 18-month follow-up. Employment and enrollment in education will be identified by using register data. Hours in competitive employment will be extracted from an extended version of the Danish Register for Evaluation of Marginalization (DREAM) database administered by the National Labor Market Authority [30]. The DREAM database contains information on employment, sickness leave, and education eligible for state education grants, disability pension, social security, and sickness benefits. The register covers the entire population, and data can be linked to a range of different registers, including the Danish income register, making it possible to obtain the exact number of employment hours. Data on education will be extracted from education statistics hosted by Statistics Denmark (http://www.statbank.dk) and supplemented by data from interviews for more detailed information on part-time studies.

The primary outcome will be supported by several other secondary and explorative outcome measures. Secondary outcomes are work or education at some point during the follow-up period (yes/no), days to first employment or beginning of education, cognitive impairment, functional level, self-esteem, and self-efficacy assessed at baseline and 18-month follow-up. Data on employment and education will similarly be extracted from registers. Furthermore, semi-structured interviews using the Personal and Social Performance (PSP) scale [31] and the Brief Assessment of Cognition in Schizophrenia [32] will be used to assess cognitive impairment and functioning. Standardized validated survey instruments, including the Rosenberg self-esteem scale [33] and the General Self-Efficacy scale [34], will be used to assess self-esteem and self-efficacy. All secondary outcomes and the assessment instruments used are outlined in Table 2.

**Table 2 Tab2:** Primary and secondary outcomes and data collection

Outcomes	Source of collection	Assessment	Baseline	18-month follow-up
Primary outcome	Register-based/Interview	Hours in competitive employment or education in follow-up period		X
Secondary outcomes	Register-based	Competitive employment or education at some point during follow-up period		X
	Register-based	Days to first employment or beginning of education		X

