### Sample size and power calculation

No previous IPS trials or similar studies have been conducted in Denmark that could contribute to an estimation of the expected average number of hours of work among participants in the IPS intervention. A European IPS multicenter trial found a difference between the IPS group and the control group (vocational services) of 150 h in competitive employment in an 18-month follow-up period, and standard deviation was 500 [19]. A difference of 150 h in competitive employment or education is considered clinically relevant. If the outcome within each intervention group is normally distributed with a standard deviation on 500 and with a true mean difference of 150 between the intervention and the control group, the present trial will need 250 participants in both intervention arms and additionally 250 control participants to be able to reject the null hypothesis that the population means of the experimental and control groups are equal with probability (power) of 80 %. The type I error probability associated with the null hypothesis is 1.25 %. A type I error of 1.25 % was chosen to give the possibility to make four comparisons: (1) IPS versus service as usual, (2) IPS versus IPS enhanced, (3) IPS enhanced versus service as usual, and (4) IPS + IPS enhanced versus service as usual. If we encounter difficulties in recruiting 250 participants to each group, we will exclude comparison (4) as a primary comparison. With three primary comparisons, we use a type I error of 1.67 % in the sample size calculation, accumulating a sample size of 236 patients in each group. Power calculations on calculations of the secondary outcome measures were carried out (Table 5) and indicate that a sample size of 250 patients per group would be adequate to detect relevant significant differences.

**Table 5 Tab5:** Power calculation

Outcome measure	δ expected difference in mean	σ expected standard deviation	α	Power	Reference
Days to first employment or beginning of education	68	45	0.0125	1.000 (*t* test)	Bond et al. [8] (2008),
Cognitive function	0.3	0.7	0.0125	0.989 (*t* test)	McGurk et al. [13] (2005)
The Brief Assessment of Cognition in Schizophrenia [32]					
Function measured with Personal and Social Performance (PSP) scale [31]	7	14	0.0125	0.999 (*t* test)	Kawata et al. [31] (2008). Nasrallah et al. [46] (2008) (No IPS studies use PSP scale. δ is estimated)

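### The only work-history term named for the primary model is a 2-month yes/no split; adding register employment hours before randomization would probably gain some precision

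*Protocol article*

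**What the plan says.** - **Prognostic value.** Randomization, protocol article: "Previous research has shown an effect of sex and of work history on vocational outcomes". The allocation is therefore stratified by sex, work history, work readiness (match category) and site.
- **Form of the work-history stratifier.** It has two levels: "work history (more or less than 2 months of competitive employment during the last 5 years".
- **Covariates.** Data analysis plan: "All models will be adjusted for the stratification variables". No other covariate is named, and none is ruled out.
- **Model.** Continuous outcomes, including the primary one, are analyzed with generalized linear models. There is a fallback: "In situations in which the continuous measure is non-normally distributed, a non-parametric model will be used".
- **Source of hours.** Outcome and assessments describes a whole-population register that can be linked to income data, and says of this linkage that it works by "making it possible to obtain the exact number of employment hours". Education comes from separate statistics, "supplemented by data from interviews for more detailed information on part-time studies".
- **Timing.** Table 2 marks the primary outcome at 18 months only. Table 3 plans baseline values for some other register measures (social benefits, use of mental health services).
- **Size.** Sample size and power calculation: 150 h difference, SD 500, type I error 1.25 %, 80 % power, 250 per arm.

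**The concern.** A cut at 2 months in 5 years gives the same level of the work-history term to someone with 3 months of work and someone with 4 years. If hours worked before entry predict hours worked afterwards, the split discards part of that information, and the part discarded stays in the residual variance of the primary comparison.

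Two features of the trial make this worth raising. First, the sample size calculation gives a power very close to its 80 % target and claims no gain from covariates. Second, the eligibility criteria do not expressly exclude people already working or studying. The primary outcome counts hours from baseline, so entry status may matter, yet no covariate for it is named. What is at stake is precision and power. The validity of the test is not in question.

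**Working it through.** **Inputs from the article.** Difference 150 h; SD 500 h; α = 0.0125 per comparison; 250 per arm; equal allocation. Sidedness is not stated. Two-sided is used because one-sided gives 212 per arm and does not fit the stated 250.

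**Step 1: reproduce the plan's figure.**
n per arm = 2(z₁₋α/₂ + z₀.₈)² (SD/δ)² = 2(2.498 + 0.842)² (500/150)² = 248. A t-test calculation gives 250, as stated. Power at 250 per arm is 0.804 by the normal approximation and 0.801 by the t-test.

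**Step 2: effect of an added covariate.** Let R² be the share of the variance left after stratum adjustment that prior hours would explain. The article gives no such figure, so a range is assumed. 500 h is taken as the SD after stratum adjustment.
- Residual SD = 500√(1 − R²)
- SE = residual SD × √(2/250)
- Power = Φ(150/SE − 2.498)
- Equivalent n per arm without the covariate = 250/(1 − R²)

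| R² (assumed) | Residual SD (h) | 150/SE | Power (normal) | Power (t-test) | Equivalent n per arm |
|---|---|---|---|---|---|
| 0 | 500.0 | 3.354 | 0.804 | 0.801 | 250 |
| 0.01 | 497.5 | 3.371 | 0.809 | 0.806 | 253 |
| 0.05 | 487.3 | 3.441 | 0.827 | 0.825 | 263 |
| 0.10 | 474.3 | 3.536 | 0.850 | 0.848 | 278 |
| 0.20 | 447.2 | 3.750 | 0.895 | 0.893 | 313 |

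**Step 3: which R² is plausible?** Two illustrations, both resting on assumed correlations.

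*Normal covariate.* Splitting it with share q on one side keeps the fraction f = φ(z_q)²/[q(1 − q)] of its explained variance: 0.637 at q = 0.5 and 0.490 at q = 0.2. The further share from the continuous form is 1 − (1 − r²)/(1 − r²f). For r = 0.4 and q = 0.5 this is 1 − 0.84/0.898 = 0.065. Over q from 0.2 to 0.5:
- r = 0.2 gives about 0.015–0.02 (power 0.81)
- r = 0.4 gives about 0.065–0.09 (power 0.83–0.85)
- r = 0.6 gives about 0.17–0.22 (power 0.88–0.90)

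*Zero-inflated hours.* This simulation assumed latent correlation 0.2–0.6, 30–70 % with no prior hours and 60 % with no follow-up hours. Prior hours were added untransformed to the 2-month split. The further R² was 0.002–0.136. Applied to an SD of 500, that gives power of 0.805–0.867.

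The second illustration is closer to how hours are likely to be distributed. Its lower end is practically no gain, and its upper end stays below the 20 % row of the table.

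**The case against.** The strongest reply is that nothing in the plan is wrong. Adjusting for the stratification variables is valid and already includes a work-history term. The article does not say that only these variables will be used, and a full analysis plan could add others. This stands, and it limits the point to a suggestion about efficiency.

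A reader might infer more than the article supports:

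- **That exact prior hours are available for everyone.** The register description concerns the follow-up outcome, and no look-back period is given. The stratifier needs 5 years of work history, but its source is not stated. With a first randomization in October 2012, a 5-year window would need hours from October 2007, and nothing shown says the hours data go back that far.
- **That prior hours are a baseline version of the primary outcome.** The outcome is employment or education. Exactness is claimed for employment hours only, and the article expects many participants to aim for education. This weakens the link.
- **That precision is certainly lost, by a known amount.** No correlation is given. Match category, a measure of work readiness, is also a stratifier and may already absorb part of what prior hours would explain.
- **That power is 80 % with no reserve.** The SD of 500 comes from an external trial and enters an unadjusted comparison of means. If 500 h is the SD before adjustment and the strata explain 10 % of the variance, power is already about 0.85 by the formula above.

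The gain shown also belongs to the generalized linear model. Hours are likely to be skewed, and the article does not say how any covariate would enter the non-parametric fallback.

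These objections reduce the size and certainty of the gain. They do not remove the reason for the addition: the plan calls work history prognostic, names one coarse term for it, and uses a data source that can supply a finer one.

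**Conclusion.** The point holds as an improvement in efficiency and does not show an error. The planned adjustment is valid but probably gives up some precision on the primary outcome. Over an assumed further R² of 1 to 20 %, power for 150 h at 250 per arm would rise from 0.80 to between about 0.81 and 0.89; with zero-inflated hours the gain may be close to nothing.

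This rests on three assumptions: 500 h is the SD after stratum adjustment, the register holds employment hours for a period before randomization, and the generalized linear model is the analysis used.

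**What to change.** Keep all the stratification variables in the primary model. Before unblinding, prespecify in addition:

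1. One continuous baseline covariate: register employment hours over a fixed pre-randomization window that the register covers for all participants, for example 12 months. Use a form that allows zeros, such as log(1 + hours), because a plain logarithm is undefined for people with no hours. One window is enough; 12-month and 5-year totals would overlap.
2. An indicator for being in work or enrolled in education at randomization.

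State also whether and how these covariates enter if the non-parametric fallback is used.

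The cost is one extra register extraction and a few lines in the analysis plan. First confirm how far back the hours data reach, since this decides the window. At the article's date recruitment was still under way (480 randomized by January 2015) and the analysis is planned with coded groups, so as of that date the addition could still be prespecified.
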